#### Health economic analysis

For the health economic analysis a cost-utility analysis will be undertaken from the NHS and personal social service perspective. Due to the importance of carers for patients with post-stroke depression, a supplementary analysis will be undertaken, taking a societal perspective. Costs and utilities will be estimated for individual patients using data collected at baseline and follow-up, based upon responses to EQ5D and resource use questionnaires, combined with standard cost and valuation sources [63–65]. Costs will include intervention costs and health care resource use. Questionnaires will be tested as a method for collecting resource use data and information on carer time.

Participants who do not have moderate or severe language problems will be asked to complete the standard version of the EQ5D as well as an amended picture-based version that is intended to be accessible to people with aphasia. This has not been validated but has been used in studies with similar patient populations [60, 66, 67]. Participants who do have moderate to severe language problems will be asked to complete the accessible version of the EQ5D. In addition, for participants who have carers, the carer will be asked to complete a standard EQ5D by proxy [60]. This will allow us to test alternative methods for collecting data from which to calculate quality-adjusted life years (QALYs) relevant for the patients included in the study. Utility scores based upon EQ5D responses will be calculated for patients at baseline and follow-up and QALYs will be calculated using the area under the curve defined by the scores and straight line interpolation.

Differences between costs and QALYs in the two groups will be described and the incremental cost-effectiveness ratio will be calculated. A trial-based analysis will be supplemented by an analysis using a simple decision analytic model, which will be used to estimate the cost-effectiveness of the intervention over the lifetime of the patients. This will be populated using the trial data plus information from the literature where required. Whilst this analysis will allow the estimation of lifetime cost-effectiveness and associated cost-effectiveness acceptability curves through the use of probabilistic sensitivity analysis, it is recognised that this will represent only a provisional estimate of the potential cost-effectiveness of the intervention, due to the nature of the feasibility study. The key outcome from the economic evaluation will be provided by a value of information analysis which will allow us to identify those model parameters that are the best candidates for further research [68]. This will be done by estimating expected values of perfect information for each parameter, which in essence identifies the maximum return for additional research [69].

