#### Sample size calculation

As a feasibility study, this is not powered for efficacy and no formal interim analyses of efficacy are planned. Rather, the sample size for a feasibility study should be adequate to estimate the uncertain critical parameters (standard deviation for continuous outcomes; consent rates, event rates, attrition rates for binary outcomes) needed to inform the design of the definitive RCT with sufficient precision. The sample size of 60 patients allows standard deviation for continuous outcomes, such as the PHQ-9 and VAMS Sad, to be estimated to within precision of approximately ±19 % of its true value (with 95 % confidence). Allowing for 15 % attrition by 6-month post-randomisation follow-up, 72 participants need to be recruited. To achieve the target sample size of 72, over the 12-month recruitment period, with three centres we need to randomise two participants per centre per month.

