## Discussion

This pilot trial is designed to assess the feasibility of a definitive multicentre RCT to evaluate the clinical and cost-effectiveness of BA for treating post-stroke depression. Ethical approval was obtained on 29 January 2015. Recruitment to BEADS started in May 2015 and is planned to run until the end of April 2016.

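### The objective is to value the definitive trial, but the stated method gives perfect information one parameter at a time, which is not the ceiling for a trial that informs several parameters together

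*Protocol article*

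**What the plan says.** The Objectives section gives five grounds for judging whether to proceed to a definitive trial. The fifth is the potential value of conducting that trial, based on value of information analysis. The thing to be valued is a whole study.

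The Health economic analysis section gives this analysis a high status: "The key outcome from the economic evaluation will be provided by a value of information analysis". The purpose stated there is narrower, namely to "allow us to identify those model parameters that are the best candidates for further research". The method follows: "This will be done by estimating expected values of perfect information for each parameter, which in essence identifies the maximum return for additional research". No other value of information quantity is named.

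The Discussion describes the future study as a "definitive multicentre RCT to evaluate the clinical and cost-effectiveness of BA for treating post-stroke depression". On the present data, the Health economic analysis section says: "Costs and utilities will be estimated for individual patients using data collected at baseline and follow-up". It also plans a simple decision model with probabilistic sensitivity analysis.

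**The concern.** A definitive RCT of clinical and cost-effectiveness would reduce uncertainty about treatment effect, utilities and costs at the same time. Values of perfect information for single parameters do not describe that. Resolving one parameter alone may rarely change the preferred option, while resolving several together may change it often. Single values can therefore be close to zero when the group has material value.

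The maximum-return wording invites a reader to take the per-parameter figures, or the largest of them, as the most that further research could yield. That is correct for research confined to one parameter. It is not correct for the trial named in the Objectives. What is at stake is whether the stated analysis answers one of the five grounds listed under the primary objective.

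**Working it through.** **Figures in the plan.** The article gives no figure for the value of information analysis, so there is none to reproduce. All inputs below are assumptions chosen to show the range.

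**Model.** There are two options. Incremental net benefit (INB) per patient is normal with mean μ. Its uncertainty is the sum of two independent contributions, QALYs (SD £400) and costs (SD £300). The joint SD is √(400² + 300²) = £500.

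**Formula.** For a parameter or group contributing SD s, the expected value of perfect information about it is s × [φ(z) − z × Φ(−z)], with z = |μ|/s. Here φ and Φ are the standard normal density and distribution function.

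**Worked case, μ = £500.**
- QALYs alone: z = 1.25; 400 × (0.18265 − 1.25 × 0.10565) = £20.2
- Costs alone: z = 1.667; 300 × (0.09948 − 1.667 × 0.04779) = £5.9
- Both together: z = 1; 500 × (0.24197 − 1 × 0.15866) = £41.7

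**Range over the assumed mean (£ per patient).**

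| Mean INB | QALYs alone | Costs alone | Sum of singles | Joint | Joint / largest single | Joint / sum |
|---|---|---|---|---|---|---|
| 0 | 159.6 | 119.7 | 279.3 | 199.5 | 1.25 | 0.71 |
| 200 | 79.1 | 45.3 | 124.5 | 115.2 | 1.46 | 0.93 |
| 500 | 20.2 | 5.9 | 26.2 | 41.7 | 2.1 | 1.6 |
| 1,000 | 0.80 | 0.03 | 0.84 | 4.2 | 5.3 | 5.1 |

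The joint value exceeds the largest single value in every row. The sum is too high when the decision is near indifference and too low when it is fairly clear, so adding the singles is not a repair.

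**Check with a non-additive model.** INB was set to £20,000 × utility gain × duration − cost, with 2,000,000 draws in each of seven assumed scenarios. Mean utility gain was 0.02 to 0.08, mean duration 1 year, and mean incremental cost £600 to £1,200. With all three parameters learned together, the joint value was 1.4 to 7.5 times the largest single value and 0.6 to 5.4 times the sum. The first ratio is lowest at 334.54/238.9 = 1.4, where mean INB is about zero.

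**The case against.** The strongest reply is that the sentence is sound in its own place. It follows directly on the aim of finding the best candidate parameters. Per-parameter perfect information is the standard tool for that, and each value is indeed the maximum return for research on its own parameter. The Abstract gives the same purpose. This stands as a defence of ranking. It does not reach the Objectives section, which asks for the value of a trial, and the article names no other quantity to answer that.

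A second reply is that a condensed article may leave detail to a fuller plan. This stands for scaling to the affected population, the decision horizon and comparison with trial cost, so none of these is held against the plan. Overall EVPI may also appear in a fuller document. The point here rests on what the article does state: a per-parameter method, and the meaning attached to it.

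A third reply is that the size is invented and could be small. This also stands. With about 60 evaluable patients, uncertainty may be wide relative to the mean. Near indifference the largest single value is already 80% of the joint value (159.6/199.5). In the £1,000 case both amounts are small per patient.

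A reader might also infer that the plan is biased towards rejecting a definitive trial. The document does not support that. Perfect information is itself an upper bound, whereas a real trial yields sample information at a cost, so the error against the trial's net value could go either way. Nor does the article attach a threshold to the result. The Data analysis section omits value of information when it lists what will determine feasibility, and the lifetime cost-effectiveness result is described as provisional.

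**Conclusion.** The point holds as a mismatch between a stated objective and the stated quantity. Per-parameter perfect information ranks parameters properly. It does not bound the value of an RCT that informs effect, utilities and costs together, and the maximum-return wording is too broad for that use.

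That the joint value is never below any single value is general. The size of the gap is not: under the assumed SDs and independence, it runs from 1.25 times the largest single value at a mean net benefit of £0 to 5.3 times at £1,000. The documents give no inputs that would place this trial in that range. The finding does not show that the go/no-go decision would be wrong, or that it would lean against further research.

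**What to change.** From the probabilistic draws already planned, also report:
- overall EVPI; and
- EVPPI for the group of parameters that a definitive RCT would measure (treatment effect, EQ-5D utilities and resource use).

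Use these for the objective on the value of conducting the definitive trial, and keep per-parameter values for ranking only. Reword the maximum-return sentence so that it applies to research on the parameter or group concerned. If a fuller analysis plan already contains these quantities, the Health economic analysis text need only say so.

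The cost is a little extra analysis of existing simulation output. No new data are needed.

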#### Qualitative data analysis

The qualitative data will be analysed thematically, using a framework analysis approach [70] to allow us to explore both a priori and emergent themes across the dataset. The transcripts from the patient and carer interviews will be explored to understand their experiences of being recruited into the trial, the study procedures and for those in the intervention group, their experiences of the BA therapy, acceptability and any perceived impacts or benefits. The transcripts of the interviews with the therapists will be examined to understand the feasibility and acceptability of the study and intervention procedures in more depth, with a view to informing the design of any future trial and subsequent intervention.

#### Anticipated risks and benefits

This study is not an investigation of a medicinal product and entails no invasive procedures. The benefits of BA suggested by the CALM trial include improved mood [33]. No participants will have any existing treatments withdrawn. The intervention is low risk to the trial participants however, and stopping on grounds of patient safety is not anticipated. As this is a feasibility trial, it will not stop early for efficacy. The study may be stopped as a whole because of safety concerns or issues with study conduct at the discretion of the sponsor. There are no formal statistical criteria for stopping the trial early. Decisions to stop the trial early on grounds of safety or futility will be made by the Trial Steering Committee (TSC) on the basis of advice from the Data Monitoring and Ethics Committee (DMEC).

There is a risk that participants may experience some distress from being asked about their mood, but all researchers and therapists will be trained to deal with these situations. If at any point during the baseline assessment, intervention or outcome assessment the researcher or therapist is concerned about a participant, for example, severe distress or reporting feeling suicidal, then the necessary referrals will be made.

#### Suicide and suicidal intentions

The risks of suicide are inherent in the nature of the condition under scrutiny (depression), and for the purposes of this study are classed as adverse events. We will follow good clinical practice in monitoring for suicide risk during all encounters with trial participants. Where any risk to patients due to expressed thoughts of suicide is encountered, we will follow local suicide protocols for each participating site.

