More specifically, if during the trial there is a patient allocated to the BEADS intervention who subsequently needs clinical psychology input (as per the protocol of the local service) then the BEADS therapist (AP/PWP) will discuss this with the clinical psychologist or clinical lead and the patient and will agree what is best for the patient. If it is agreed that the patient needs immediate clinical psychology input then they would be withdrawn from the BEADS intervention and they will see the clinical psychologist, or be referred to alternative provision, as appropriate to that patient. The patient will be withdrawn from the intervention but not the overall trial, i.e. we will still be able to collect outcome data from them. We will record the number of patients who we withdraw from the BEADS intervention because of a conflict with clinical services.

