### Trial treatment and regimen

#### Intervention arm—behavioural activation therapy

Behavioural activation (BA) therapy is a structured and individualised treatment which aims to increase people’s level of activity, particularly the frequency of pleasant or enjoyable events, in order to improve mood. Participants randomised to receive BA will be treated at their place of residence by an assistant psychologist at two centres or low-intensity psychological wellbeing practitioner (PWP) at one centre. They will be offered a maximum of 15 sessions of BA over 4 months, with an expected average of 10 sessions. Therapy sessions will be delivered face to face on an individual basis, at the participants’ residences and will last about 1 h. A BA treatment manual was developed for CALM based on the behavioural component of CBT for depression in stroke patients [22, 24], behavioural therapy with older people [47] and guidelines on conducting therapy with people who have aphasia [35, 47, 48]. For this trial, this therapy manual will be further revised to cover BA with stroke patients who do not have aphasia and will provide examples and practical guidance relevant to all stroke patients.

The intensity and duration of therapy is based on a study of CBT with stroke patients [24] and is informed by the CALM study in which participants received an average of nine 1-h sessions over 3 months [33]. Experience and criticism of the CBT trial [24] was that therapy was too short. The trial of BA for treating depression in primary care provided 12 sessions over 3 months [49] but this was not in a stroke sample and patients with communication and/or cognitive difficulties may require a longer duration of therapy. The duration of therapy has been increased from 3 to 4 months because the CALM study showed that it was difficult to complete sessions in 3 months due to non-availability of the participant and short-term illness. Extending therapy to 4 months will also allow flexibility to provide therapy visits to support maintenance, as might be provided in clinical practice. The number of therapy sessions will vary according to the needs of the individual and their progress in therapy. The intensity of treatment will be negotiated between the therapist and the participant, based on their progress in achieving their therapy goals.

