#### Control arm—usual care

Participants in the usual care group will follow the current care pathway. Participants will receive all other services routinely available to them as local practice but will have no contact with the trial therapist. This group is the control arm and their care will be recorded to document usual care to inform the design of the definitive trial. Stroke survivors are admitted to hospital, usually to a stroke unit. On discharge, they may receive input from an early supported discharge team or input from a community stroke or rehabilitation team. Availability of psychological support in the community is inconsistent and likely to vary widely across the country as highlighted by the Stroke Improvement Programme [50]. The CALM trial [33] found that at the 3-month follow-up, only 14 % of participants had received mental health treatment in the past 3 months (from a mental health nurse, counsellor, psychologist or psychiatrist) and this decreased to 10 % at the 6-month follow-up. Although Improving Access to Psychological Therapies (IAPT) have extended their remit to include people with physical health problems [51, 52] the current rate of uptake by stroke patients is unknown.

Only patients not currently receiving psychological intervention are eligible to be recruited to BEADS. The provision of clinical psychology varies. Some sites have a full-time clinical psychologist providing input to both hospital and community services and other sites can access this service but do not have dedicated provision. IAPT services will consider treating stroke patients if referred, but this rarely occurs. GPs may prescribe anti-depressants. Only those with severe mental health problems are referred to psychiatrists. The content of usual care is decided locally by the clinical team as to what this will be, as per local services.

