As part of the feasibility analysis, the effect size for the 6-month PHQ-9 outcome and the difference in mean scores (and associated 95 % confidence intervals [62]) between groups will be estimated. A marginal or random effects model will be used to allow for any clustering by therapist, with baseline PHQ-9 as a covariate to check that the likely effect is within a clinically relevant range, and this will be used as confirmation that it is worth progressing with the definitive trial. The accuracy of the cut-off of the VAMS Sad in comparison with the PHQ-9 will also be checked. This information along with the acceptability of the study design and protocol to patients and carers; the safety of the intervention; patient recruitment and consent/retention rates will enable us to determine whether or not the definitive RCT is feasible.

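### Suicide risk counts as an adverse event and is looked for at every trial encounter, but BA participants have about 10 more encounters on average, so raw safety counts by arm risk differential ascertainment

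*Protocol article*

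**What the plan says.** Under Suicide and suicidal intentions, the risks of suicide are treated as part of the condition and "for the purposes of this study are classed as adverse events". The same section gives the rule for finding them: "We will follow good clinical practice in monitoring for suicide risk during all encounters with trial participants". Anticipated risks and benefits names the occasions on which distress or suicidal feelings would be noticed: "If at any point during the baseline assessment, intervention or outcome assessment the researcher or therapist is concerned about a participant". Of these three, intervention exists only in the BA arm.

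The two arms have very different contact with trial staff. For BA: "They will be offered a maximum of 15 sessions of BA over 4 months, with an expected average of 10 sessions". Usual-care participants "will have no contact with the trial therapist" (Control arm—usual care). Both arms have the 6-month assessment, done by a blinded researcher (Randomisation and blinding). Qualitative interviews involve eight participants per arm, so they do not alter the balance.

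Data analysis then lists, among the inputs to the progression decision, "the safety of the intervention; patient recruitment and consent/retention rates will enable us to determine whether or not the definitive RCT is feasible".

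**The concern.** Taken together, these statements make the chance that an event is seen depend on how often a participant meets trial staff, and that differs sharply by arm. With equal true risk, the stated rule tends to record more suicidal ideation and distress under BA.

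Two misreadings are then possible. A harmless intervention could look as if it provokes suicidal thoughts, or a real excess could be put down to extra contact. Because the protocol itself regards suicide risk as inherent in depression, a count from the BA arm alone cannot separate the effect of BA from that of the illness. That needs a control arm observed in the same way. The safety input to the progression decision would be hard to interpret in either direction.

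**Working it through.** **Figures in the plan.** The target is 72 participants in equal proportions, so 72/2 = 36 per arm. The target reproduces: 3 centres × 12 months × 2 per month = 72, and 60/(1 − 0.15) = 70.6, rounded up to 71, close to 72. No stated figure is in dispute.

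**Encounters after randomisation, per participant**
- Usual care: 0 therapist sessions + 1 assessment = 1.
- BA at expected attendance: 10 + 1 = 11.
- BA at the ceiling: 15 + 1 = 16.
- Difference: about 10 on average, at most 15.

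**Illustration 1: the 6-month visit picks up nothing from earlier months.** Assume the same chance p of an event being detected at any encounter, in both arms, with encounters independent. The documents give no p, so a range is shown. The proportion of participants with at least one detected event over k encounters is 1 − (1 − p)^k.

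| p | Usual care, k = 1 | BA, k = 11 | BA, k = 16 | Ratio, 11 vs 1 |
|---|---|---|---|---|
| 0.01 | 1.0 % (0.4 of 36) | 10.5 % (3.8) | 14.9 % (5.3) | 10.5 |
| 0.05 | 5.0 % (1.8) | 43.1 % (15.5) | 56.0 % (20.2) | 8.6 |
| 0.20 | 20.0 % (7.2) | 91.4 % (32.9) | 97.2 % (35.0) | 4.6 |

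This is the extreme case.

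**Illustration 2: earlier episodes can be recalled at 6 months.** Let a fraction T of participants in each arm have an episode, q be the chance that it is reported at 6 months, and s = 0.80 the assumed chance that it is detected at BA sessions.
- Detected in usual care: T × q.
- Detected in BA, sessions and 6-month report pooled: T × [1 − (1 − q)(1 − s)].
- T cancels, so the ratio is [1 − 0.20(1 − q)]/q.

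Results:
- q = 0.25: 0.85/0.25 = 3.4
- q = 0.50: 0.90/0.50 = 1.8
- q = 0.75: 0.95/0.75 = 1.27
- q = 1.00: 1.00/1.00 = 1.0

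A 6-month question asked of both arms thus narrows the gap. It does not close it if session detections stay in the BA count, unless recall is complete.

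**With the comparison restricted to the common occasion.** Both arms yield T × q, one opportunity each, so the expected ratio under equal true risk is 1.0, provided that recall is the same in both arms.

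**The case against.** The strongest reply is that the sections on risks and on suicide describe a duty of care, with referral and local protocols, and not a scheme for collecting adverse events. The article condenses a fuller protocol. A standard 6-month adverse-event query in both arms is compatible with every word of it, and how events are tabulated may properly be left to the SAP. The article states no between-arm safety test: its analysis is descriptive, there are no statistical stopping criteria, and the DMEC reviews serious adverse events thought to be treatment-related, which is a case-by-case judgement.

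Much of this stands, and it limits the point to a risk. It does not remove it. The article itself classes suicide risk as an adverse event, ties its detection to encounters, and lists safety as an input to the progression decision. A symmetric query in the full protocol would not take the BA-only session detections out of a pooled count, and an SAP cannot recover usual-care events that nobody elicited.

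A reader might infer more than the documents support:
- *That the safety comparison is already biased, perhaps tenfold.* No such comparison is specified, and ratios near ten need independent encounters, a small assumed p and no recall at 6 months.
- *That BA participants have 10 to 15 more encounters.* Ten is the expected average and 15 the ceiling.
- *That the count of withdrawals is a second asymmetric safety measure.* The sentence "We will record the number of patients who we withdraw from the BEADS intervention because of a conflict with clinical services" concerns delivery. Usual-care participants have no BEADS intervention to leave, so the count can exist only in the BA arm.
- *That the definitive trial would inherit the scheme.* The article does not say so, and the acceptability of research procedures is among the things this trial is meant to examine.

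**Conclusion.** The point holds as a risk of differential ascertainment that arises from stated rules. BA participants are expected to have about 10 more post-randomisation encounters (at most 15 more) at which suicide risk is monitored and would count as an adverse event. A higher raw count under BA could therefore not be attributed to BA.

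The direction needs only that sessions detect some events which the 6-month visit would miss. The size cannot be derived from the documents. Every ratio shown rests on assumed detection and recall, and the excess vanishes if 6-month recall is complete. Safety is one of several inputs to the progression decision, so this weakens one strand of it and not the whole.

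**What to change.** State in the protocol or SAP that any between-arm safety summary uses only events elicited identically in both arms over the 6 months. The sources are the healthcare resource use questionnaire already planned for the 6-month assessment, plus the same fixed adverse-event questions at that visit, asked after the outcome measures. Report events detected at BA sessions separately, as description of the BA arm that is not compared with usual care. Keep the withdrawal count as a delivery-feasibility measure. If the full protocol already has a symmetric query, one clarifying sentence on reporting is enough. Immediate handling of risk at encounters is unchanged.

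The cost is some wording and a few questions at an existing visit. There are three downsides:
- Six-month recall will miss some transient events.
- The questions carry a slight risk of unblinding the assessor, which asking them last limits.
- Participants lost before 6 months contribute nothing to the comparison. If the planned 15 % attrition applied equally to each arm, that is 0.15 × 36 = 5.4, or about 5 per arm.
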